### Implementation {16c}

The allocation sequence is generated by a third party who is not involved in the study. The physician investigators enroll the participants, and based on the results of the pre-intervention evaluation, the participants are assigned to the sub-studies. The rTMS administrator verifies the electronic data capture system to determine the participant’s assigned group.

### Assignment of interventions: blinding

#### Who will be blinded {17a}

This study is conducted as a single-blind clinical trial with a blinded observer; the rTMS administrator is aware of the participant’s assigned group, while both the participant and assessor are unaware of which treatment is being implemented. The evaluation is performed by an investigator who does not administer rTMS, to ensure that the assessor remains blinded.

### Procedure for unblinding if needed {17b}

This is a single-blind study; therefore, the assessors and participants will not be informed of the study arm. However, unblinding should be considered in cases of serious medical emergencies. In the event of a serious medical emergency, unblinding will be performed only if information regarding the stimulation protocol affects the participant’s treatment. Unblinded participants will not be permitted to continue within the study.

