### Criteria for discontinuing or modifying allocated interventions {11b}

The criteria for discontinuing the intervention are as follows:Voluntary discontinuation by the participant: Participants have the freedom to withdraw from the trial at any time without providing an explanation, and this will not affect their future treatment.Missed follow-up visits.Discontinuation due to a significant adverse event or if the participant or legal representative requests termination due to adverse events.Based on the investigator’s judgment, the progression of a clinical trial may be deemed unsuitable.Significant protocol violation or deviation from inclusion/exclusion criteria during the clinical trial.Study adherence < 80%.$$\text{Adherence }\left({\%}\right)= \left(\frac{\text{Actual number of rTMS sessions performed}}{\text{Total required rTMS sessions}}\right)\times 100$$

Modifications of allocated interventions are not considered.

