### Outcomes {12}

Pre-intervention evaluations will be conducted within 3 days before the initial intervention session. Post-intervention evaluations will be conducted within 48 h after the final intervention session. Follow-up evaluations will be conducted 2 months after the intervention concludes. The primary outcome is the difference in TUG time between the pre- and post-intervention evaluations. Secondary outcome variables include the TUG measured at follow-up evaluations. Additionally, the TUG-Cog, MDS-UPDRS Part III, New Freezing of Gait Questionnaire (NFoGQ), Digit Span, trail-making test, transcranial magnetic stimulation-induced motor-evoked potential (TMS-induced MEP), diffusion tensor imaging (DTI), and rsfMRI are assessed pre-intervention, post-intervention, and at follow-up to investigate the effectiveness of personalized rTMS.

The TUG assesses ambulatory functions, including gait, balance, mobility, and fall risk. In the TUG, the participants are instructed to rise from a chair, walk to a traffic cone located 3 m away at a comfortable pace, return to the chair, and sit down. The TUG-Cog involves the simultaneous execution of the TUG test and serial subtraction in three, starting from a randomly selected number between 80 and 100 [34]. The TUG-Cog is designed to provide a comprehensive assessment by incorporating both motor and cognitive tasks. The TUG and TUG-Cog are each measured twice, and the mean values are utilized for analysis. During the TUG and TUG-Cog, the participants wore shoes equipped with a smart insole (Gilon Gait Data Collector & Analyze MD, Gilon Inc., Gyeonggi, Republic of Korea). The smart insole measures gait parameters including stride length, step count, cadence, velocity, distance, swing ratio, and foot plantar pressure (heel/mid/toe). The stride lengths of the TUG and TUG-Cog are utilized to assign sub-studies and evaluate the efficacy of the intervention. During the mid-intervention evaluation, the TUG is conducted without smart insoles.

The MDS-UPDRS part III assesses the motor symptoms of PD using 18 items, with each item scored on a scale of 0 to 4 [46]. Higher scores indicate more severe symptoms. The NFoGQ consists of nine items designed to assess the severity of freezing of gait (FoG) and gait disturbance [47]. The NFoGQ has demonstrated reliability in measuring both the severity of FoG and its functional impact in patients with PD.

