### Participant timeline {13}

Figure 1 presents a comprehensive flowchart of the study process, including the allocation phase. After enrollment and screening, a pre-intervention evaluation is conducted. Based on the pre-intervention evaluation, participants are classified into sub-studies and allocated to either the experimental or control group. The first rTMS session takes place within 3 days of the pre-intervention evaluation. The initial 5 interventions are administered within 2 weeks, with a mid-intervention evaluation employed within 24 h following the fifth session. Subsequently, an additional 5 rTMS sessions are administered over the next 2 weeks, and within 48 h of completing all intervention sessions, an immediate post-intervention evaluation is conducted. Follow-up evaluation is performed 2 months after the completion of the intervention, marking the end of the study. The total study duration is anticipated to be approximately 12–14 weeks. The timelines for both the experimental and control groups in the sub-studies are identical (Table 2).

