**Assessments:**							
* TUG, TUG-Cog*		X		X		X	X
* Gait analysis*		X				X	X
* MDS-UPDRS Part III*		X				X	X
* NFoGQ*		X				X	X
* Cognitive function test*		X				X	X
* TMS-induced MEP*		X		X		X	X
* Brain MRI*		X				X	X
* Adverse event measure*		X	X	X	X	X	X

*HF rTMS* High-frequency repetitive transcranial magnetic stimulation, *M1-LL* Primary motor cortex in the lower limb, *DLPFC* Dorsolateral prefrontal cortex, *M1-UL* Primary motor cortex in the upper limb, *TUG* Timed-Up and Go, *TUG-Cog* Timed-Up and Gg under cognitive dual-task condition, *MDS-UPDRS* Movement Disorder Society-Unified Parkinson’s Disease Rating Scale, *NFoGQ* New Freezing of Gait Questionnaire, *TMS-induced MEP* Transcranial magnetic stimulation-induced motor-evoked potential, *MRI* Magnetic resonance imaging

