### Methods in analysis to handle protocol non-adherence and any statistical methods to handle missing data {20c}

All participants involved in this study and those undergoing intervention are included in the intention-to-treat (ITT) set. Safety analyses are conducted based on the ITT dataset. Participants in the ITT set who undergo the TUG test at both pre- and post-intervention evaluations are categorized as the full analysis set (FAS). Efficacy analysis will be based on the FAS. Those in the ITT set who successfully complete the study with no significant protocol violations are classified into the per-protocol (PP) set. Efficacy analyses within the PP set are conducted alongside the FAS. In the event of disparities between the FAS and PP analyses, the reasons behind such difference will be investigated. For missing values, data will be analyzed using the last-observation-carried-forward method, assuming that the most recent observation was obtained at that time point.

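### A participant unblinded in a medical emergency is removed from the study, not only from rTMS, so the primary TUG and scheduled safety visits are given up without need

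*Protocol article*

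**What the plan says.** **Unblinding.** Procedure for unblinding if needed {17b} sets two conditions. There must be a serious medical emergency, and knowledge of the stimulation protocol must matter for the participant's care. It then states: "Unblinded participants will not be permitted to continue within the study".

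**Efficacy set.** Section {20c} bases efficacy on those in the ITT set "who undergo the TUG test at both pre- and post-intervention evaluations are categorized as the full analysis set (FAS"). Missing values are handled by last observation carried forward. Safety is analysed in the ITT set.

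**Visits.** Table 2 schedules the TUG at baseline, mid-intervention (t6), post-intervention (t12) and the 2-month close-out (t13). The row "Adverse event measure" is marked at every time point from baseline to close-out.

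**Blinding.** Who will be blinded {17a} has the evaluation done by someone who does not give rTMS. Participant and assessor are both meant to be unaware of the arm.

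**Adverse events.** Adverse event reporting and harms {22} asks for the dates, causality and final outcome of each event.

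**The concern.** Stopping rTMS and stopping measurement are separate decisions. After a serious emergency, ending stimulation may well be right. Section {17b} goes further and ends participation, and it gives no reason for ending measurement.

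Two things are at stake. The first is the primary comparison, the change in TUG from pre- to post-intervention. A randomised participant would be missing from it for a reason that arose after randomisation, which is the kind of exclusion that can weaken the balance randomisation provides. The second is safety, which the Objectives {7} name as an aim alongside efficacy. Scheduled safety assessments would end for participants who had a serious medical emergency, the group for whom follow-up is of most interest.

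**Working it through.** The document gives no expected number of unblindings, so there is no figure to reproduce. The check follows one unblinded participant through the stated rules.

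**Step 1. What the rule ends.** Section {11b} lists reasons for discontinuing the intervention, and a significant adverse event is one of them. Section {17b} refers to continuing within the study. Under these texts, a participant who stops rTMS for an adverse event and is not unblinded is not stated to leave assessment. One who is unblinded does leave. It is the unblinding, not the medical event, that ends follow-up.

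**Step 2. Consequence by time of unblinding** (visits from Table 2, set definition from {20c}).

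| Unblinded | TUG already measured | TUG lost | In the FAS? | Scheduled adverse event visits lost |
|---|---|---|---|---|
| Before t6 | pre | mid, post, 2-month | No | t6, t12, t13 and any left during treatment |
| After t6, before t12 | pre, mid | post, 2-month | No | t12, t13 and any left during treatment |
| After t12, before t13 | pre, mid, post | 2-month | Yes | t13 |

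In the first two rows the primary outcome is lost. In the third, only the 2-month TUG (a secondary outcome) and one safety visit are lost.

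**Step 3. Can the missing-data rule repair this?** No. FAS membership depends on having undergone the post-intervention TUG. A participant in the first two rows is outside the set before any carried-forward value is used, even with a mid-intervention TUG on record.

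**Step 4. Is removal needed to protect the assessment?** The assessor in {17a} does not give rTMS. The disclosure can be confined to those treating the emergency, so a TUG by an assessor who stays blind remains feasible.

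**Step 5. What happens to safety data?** The participant stays in the ITT set and so in the safety analysis. Section {22} still obtains the outcome of the event itself. What ends is the scheduled assessment that would pick up later or different events.

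**Step 6. Scale.** Section {14} plans 30 per sub-study and a 75% follow-up rate, which allows 25% loss. One removal is 1/30 = 3.3% of a sub-study and falls inside that allowance.

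**The case against.** **The trigger is narrow.** Both conditions must be met, and the trial may see no unblinding at all. This stands, and it is why the point is minor.

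**Knowing the arm could influence the TUG.** The test is a performance measure, and a participant who learns the allocation may behave differently. This stands in part. However, both arms receive active stimulation, and {11c} tells participants to expect benefit in either group. A recorded unblinding can be examined in the analysis, whereas an outcome never collected cannot.

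**The participant may be too ill to be tested.** That is possible, and the TUG would then be missing for a clinical reason. It does not justify a rule that also removes those who could be tested.

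**Safety is already covered.** Section {22} does follow the event to its outcome. It does not replace the scheduled visits.

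**A published article is condensed.** True, but this is a stated rule and not an omitted detail, and no analysis plan can recover uncollected data.

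A reader might infer two wider problems, which the document does not support:

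- **Visit timing for early stoppers.** Outcomes {12} says "Post-intervention evaluations will be conducted within 48 h after the final intervention session". Someone who stops at session 5 might therefore seem due for a post-intervention TUG almost together with the mid-intervention one. But Participant timeline {13} ties the same visit to "completing all intervention sessions, an immediate post-intervention evaluation is conducted". Both texts describe the regular ten-session course, and neither sets a rule for early stoppers. Measuring such participants at week 4 would in any case be a choice of estimand.
- **Low adherence or missed visits ending assessment.** The criteria "Study adherence < 80" per cent and "Missed follow-up visits" stand in {11b}, which concerns stopping the intervention. It does not say that assessment ends, and a low adherer with both TUGs is in the FAS.

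**Conclusion.** The point holds for the unblinding rule and is minor. Section {17b}, read with the FAS definition in {20c}, excludes from the primary comparison any participant unblinded before the post-intervention visit. It also ends that participant's remaining scheduled adverse event assessments. This rests on the plain meaning of study in {17b} and on the FAS being applied as defined.

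The number affected cannot be derived and may be zero. The document does not show that removals would differ by arm, so neither the direction nor the size of any bias can be stated. A reader might also infer a material loss of power. That is not supported, because no unblinding rate is given and such removals already belong within the planned 25% loss. The case for change is that the loss is avoidable and cheap to prevent.

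**What to change.** Amend {17b} to state that:

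- unblinding may stop rTMS, but the participant stays in follow-up;
- the post-intervention and 2-month TUG and adverse event visits go ahead where clinically feasible, done by an assessor kept blind;
- the date of and reason for unblinding are recorded;
- the participant is kept in the FAS;
- only withdrawal of consent ends follow-up.

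No change to the FAS wording is needed for those who then have both TUGs. The visits are already in Table 2, so no new assessment is added. The cost is a short amendment and site retraining. The FAS may also come to include a participant who knows their arm; the recorded unblinding allows the analysis to be repeated without them.

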## Data collection and management

### Plans for assessment and collection of outcomes {18a}

This multi-center study is conducted across five tertiary hospitals in the Republic of Korea. To ensure robust data quality, researchers from all the institutions convened multiple meetings to discuss and establish standardized assessment methods. Following these discussions, comprehensive training sessions were conducted to ensure that the assessors were well-versed in standardized methodologies. Most of the assessments used in this study are validated for both reliability and validity. Additionally, we meticulously document and disseminate protocols to conduct research evaluations, allowing for the ongoing scrutiny of evaluation methods and data collection forms.

### Plans to promote participant retention and complete follow-up {18b}

Clinical research coordinators in each hospital will communicate with the participants via phone calls or text messages to ensure their awareness and participation in upcoming evaluations and interventions.

### Data management {19}

To ensure data quality, the CI selected the clinical research organization responsible for overseeing various aspects of data management. The contract encompasses tasks, such as developing an electronic case report form (eCRF) database and implementing data management protocols. The database system is tasked with query programming, performing range checks for data values, and managing data archiving. Additionally, the data management team is responsible for creating a data validation plan, overseeing query management, coding adverse events, and reconciling serious adverse events.

### Confidentiality {27}

In accordance with the ethical guidelines, personal information and research outcomes of participants will be documented on the designated eCRF without exposing personal details such as the obligation record number and name of the participant. Access to these records is restricted to registered researchers to ensure confidentiality. The identities of the participants will be kept confidential in all instances of research presentation or publication. Additionally, any research data, including imaging data and documents, will be stored in password-protected files in a secure, locked facility. Researchers are required to retain all clinical trial-related records and informed consent forms for a period of 3 years from the conclusion of the research (Bioethics and Safety Act of the Republic of Korea), and documents beyond this retention period will be disposed of in accordance with the regulations outlined in the Personal Information Protection Act of the Republic of Korea.

### Plans for collection, laboratory evaluation, and storage of biological specimens for genetic or molecular analysis in this trial/future use {33}

Not applicable. No biological specimens are collected.

## Statistical methods

### Statistical methods for primary and secondary outcomes {20a}

Demographic data are presented as means and standard deviations for continuous variables, while frequencies and percentages are used for categorical variables. Efficacy analysis are based on the assessment of the change from pre-intervention evaluation within each sub-study. To compare the baseline characteristics between the experimental and control groups in each sub-study, Student’s *t*-test for normally distributed variables or the Wilcoxon singed-rank test for non-normally distributed variables is employed. The Shapiro–Wilk test is used to examine the normal distribution of the variables.

To evaluate the effects of time, group, and the interaction of time with the group, we employ repeated-measures analysis of variance and repeated-measures analysis of covariance for variables exhibiting a normal distribution. Non-parametric variables are analyzed using a generalized estimating equation. Statistical significance is set at *P* < 0.05. A comparison between the sub-studies is not considered.

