#### Trial design {8}

This is a prospective, exploratory, multi-center, single-blind, parallel-group, randomized controlled trial.

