### Intervention description {11a}

This study comprises two sub-studies, each designed as a two-arm trial. The participants are classified into sub-studies based on their functional reserves as follows:Motor priority group (sub-study 1): Patients with well-preserved motor function in whom motor skills have a significant impact on overall functioning; andCognitive priority group (sub-study 2): Patients with well-preserved cognitive function and notable impairment in motor function in which cognitive abilities substantially affect overall functioning.

As part of the pre-intervention assessment, the TUG and the TUG under cognitive dual-task condition (TUG-Cog) are administered. The TUG-Cog involves performing the TUG test concurrently with a cognitive task of serially subtracting the number 3. Additionally, serial 3 subtraction as a single cognitive task is performed from a randomly selected number between 80 and 100 for 20 s in the sitting position [34]. For both tasks, the correct response rate for subtraction is calculated as the time spent in seconds divided by the number of correct responses. Task-specific interference is calculated using the equation for dual-task effect (DTE) (Eq. 1) [37]. The motor dual-task effect (mDTE) is computed using stride length and the cognitive dual-task effect (cogDTE) is based on the correct response rate of TUG and TUG-Cog.1$$\text{Dual task effect} \left(\%\right)=\frac{(\text{Single task }-\text{ Dual task})}{\text{Single task}} \times 100$$

For evaluation of task prioritization during dual-task conditions, the modified Attention Allocation Index (mAAI) is employed (Eq. 2) [34]. The mAAI is calculated by subtracting the cogDTE from the mDTE, where negative values indicate an attention shift toward the motor task (motor priority), while positive values suggest an attention shift toward the cognitive task (cognitive priority).2$$\text{modified Attention Allocation Index }\left(\text{mAAI}\right)=\text{motor dual task effect}\left(\text{mDTE}\right)-\text{cognitive dual task effect }(\text{cogDTE})$$

Patients demonstrating motor priority will undergo high-frequency rTMS over the primary motor cortex in the lower limb (M1-LL), whereas those showing cognitive priority receive high-frequency rTMS over the left DLPFC. Given the substantial impairment of the motor network in the latter group, we envision a heightened reinforcement of compensatory mechanisms utilizing the cognitive network.

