### Sample size {14}

The primary outcome is the change in TUG time between pre- and post-intervention evaluations. The power of the study was set at 80%, with a significance level (α) of 5%. The clinically significant effect size (δ) was determined to be 4.9, and the expected standard deviation (σ) is estimated to be 4.0 [48, 49]. The analysis was conducted using Lehr’s formula, resulting in a required sample size of 10.6 [50].$$\text {Lehr's}\,\mathrm{formula}=\left(16/(\delta/\sigma)\right)=\left(16/(4.9/4.0)\right)^2=10.6$$

The follow-up rate was targeted at 75%, based on the conventional outpatient rehabilitation treatment criteria over a 4-week period. Therefore, the sample size for each sub-study was determined to be 30.

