## Assignment of interventions: allocation

### Sequence generation {16a}

Participants are randomly allocated to the experimental and control groups of each sub-study. A designated individual, who is not involved in this study, utilizes the www.randomization.com to generate a randomization table, ensuring a 1:1 allocation between the experimental and control groups before the enrollment of the first participant. The chief investigator (CI) maintains the confidentiality of the randomization table matching list and refrains from revealing it until the completion of the final statistical analysis, managing it securely as per protocol.

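### The test named for comparing non-normal baseline variables between the two independent arms is a paired test and does not apply

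*Protocol article*

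**What the plan says.** All of this comes from the protocol article; no separate analysis plan is shown.

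- **Purpose of the test.** Statistical methods {20a} opens the relevant sentence with "To compare the baseline characteristics between the experimental and control groups in each sub-study". It then gives Student's t-test for normal variables, and for the rest states that the "Wilcoxon singed-rank test for non-normally distributed variables is employed". 'Singed' is a misprint for 'signed'.
- **How the choice is made.** In the same section the Shapiro-Wilk "test is used to examine the normal distribution of the variables".
- **Design.** Trial design {8}: "This is a prospective, exploratory, multi-center, single-blind, parallel-group, randomized controlled trial". Intervention description {11a}: "This study comprises two sub-studies, each designed as a two-arm trial".
- **Allocation.** Sequence generation {16a} describes a randomisation table "ensuring a 1:1 allocation between the experimental and control groups before the enrollment of the first participant". No section describes matching or pairing of patients.
- **Efficacy.** Section {20a} assigns efficacy to repeated-measures analysis of variance or covariance, with generalized estimating equations for non-parametric variables. The signed-rank test has no role there, and no section names a rank-sum or Mann-Whitney test.

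**The concern.** The sentence offers two tests for one comparison, and they answer different questions. Student's t-test compares two independent groups. The signed-rank test asks whether differences within pairs are centred on zero. It is the rank counterpart of the paired t-test, not of the two-sample t-test.

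The two arms of a sub-study contain different people, and nothing links a given experimental patient to a given control patient. An analyst following the text literally would have to invent the link, most likely by row order in the data file. The p-value would then be a property of the file's sorting as well as of the patients. If the arms differ in size, even that is impossible.

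What is at stake is the baseline table: any p-value in it for a skewed variable would be either arbitrary or unobtainable.

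**Working it through.** **Step 1. Does any pairing exist?** The text on each side:

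| Needed by the signed-rank test | Found in the protocol |
|---|---|
| Paired observations, or one sample of differences | Parallel groups ({8}); two arms in each sub-study ({11a}) |
| A rule that links members of a pair | 1:1 randomisation ({16a}); no matching described |
| A within-group or within-patient use | The sentence in {20a} concerns a between-group comparison at baseline only |

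None of the three requirements is met.

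**Step 2. Arm size for an illustration.** Sample size {14} gives δ = 4.9, σ = 4.0 and 75% follow-up. It states "The power of the study was set at 80" (per cent), "with a significance level (α) of 5" (per cent).

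- Lehr's rule: 16 / (δ/σ)² = 16 / (4.9/4.0)² = 16 / 1.500625 = 10.66. This reproduces the plan's 10.6, read here as per arm.
- Allowing for follow-up: 10.66 / 0.75 = 14.2, rounded up to 15 per arm.
- Two arms: 2 × 15 = 30 per sub-study, as the plan states.

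**Step 3. What happens if the test is run as written.** Assumed data: two independent lognormal arms of 15 (log-means 2.5 and 2.8, log-SD 0.5). These values are chosen only to give skewed data; they are not from the protocol.

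| Procedure on the same 30 values | p |
|---|---|
| Rank-sum (Mann-Whitney U) | 0.263, a single value |
| Signed-rank, 5,000 random pairings: lowest | 0.012 |
| Signed-rank: 2.5th percentile, median, 97.5th percentile | 0.073, 0.208, 0.454 |
| Signed-rank: highest | 0.804 |
| Signed-rank, 15 against 14 patients | cannot be computed |

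Most pairings in this data set stay above 0.05, but some fall below it. Nothing in the data says which pairing is the right one.

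**Step 4. Is the false-positive rate inflated?** The setting was 10,000 simulated trials with no true difference, 15 per arm, arbitrary pairing and a 0.05 threshold. The signed-rank test rejected in 0.047 of trials and the rank-sum test in 0.046. There is no inflation. The fault is an arbitrary result for the one data set that the trial will have.

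**Step 5. How likely are unequal arms?** This matters only if baseline is tabulated for the full analysis set, which section {20c} limits to patients with TUG both before and after the intervention. The protocol does not say which set the baseline table uses. Assume 15 randomised per arm and independent retention with probability r. Then P(arms differ) = 1 − Σₖ [Binomial(k; 15, r)]².

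- r = 0.75 (the planned rate): 0.83
- r = 0.95: 0.63

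Under that assumption the named test would more often than not be impossible to run in a given sub-study.

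**The case against.** **It is probably a naming slip.** The test is listed beside Student's t-test for an explicitly between-group comparison, and its name is misspelt. The authors may well have meant the rank-sum test. An analyst facing unequal arms would find the error at once, because the software would refuse. This stands as a reason to rate the practical risk as low. It does not remove the point: the article names a specific procedure, that procedure does not fit, and no other section supplies the right one.

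**It is detail for an analysis plan.** Silence on baseline testing could be left to another document. A test that is named, and named wrongly, is a different matter.

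**Stronger readings that a reader might infer, and that the protocol does not support:**

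- *That the error reaches the efficacy result.* One might suppose that baseline p-values decide which covariates enter the repeated-measures analysis of covariance. Section {20a} says nothing of the kind, and the signed-rank test appears nowhere in the efficacy analysis.
- *That the test inflates false positives.* Step 4 of the check shows that it does not under arbitrary pairing with equal arms.
- *That baseline significance testing is itself the error.* Whether to test baseline balance in a randomised trial is a separate matter of reporting preference. It would arise equally if the rank-sum test had been named.
- *That every baseline variable is affected.* Only those that fail the Shapiro-Wilk test are. How many will do so is unknown and could be none.

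**Conclusion.** The point holds as a wording error with a narrow effect. Section {20a} assigns a paired test to two independent arms. As written, the test gives a result that depends on an arbitrary pairing, and no result when the arms differ in size.

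It touches only non-normal baseline variables, in both sub-studies. The primary efficacy analysis, the 5% significance level and the 30 patients per sub-study are unchanged. Severity is low.

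The finding itself rests on the design description alone and needs no numerical assumption. The simulated p-values illustrate it and depend on the assumed lognormal data. The chances of unequal arms depend on 15 per arm, independent retention and a baseline table restricted to the full analysis set.

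**What to change.** In Statistical methods {20a}, replace the signed-rank test with the Wilcoxon rank-sum (Mann-Whitney U) test for non-normal baseline variables. Alternatively, delete the baseline tests and present the two arms descriptively. Either change corrects the fault.

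The cost is one sentence. No sample size, power or efficacy calculation has to be redone, and no data collection changes.

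### The primary outcome, pre-to-post TUG change, is not tied to any one of the planned repeated-measures tests; a baseline-adjusted comparison at the post-intervention visit would fix it at no cost

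*Protocol article*

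**What the plan says.** Outcomes {12} defines the primary endpoint as one contrast: "The primary outcome is the difference in TUG time between the pre- and post-intervention evaluations". TUG at the 2-month follow-up is listed there as secondary. Sample size {14} repeats the definition ("The primary outcome is the change in TUG time between pre- and post-intervention evaluations") and sizes the trial on it: "The clinically significant effect size (δ) was determined to be 4.9, and the expected standard deviation (σ) is estimated to be 4.0", and "The analysis was conducted using Lehr’s formula, resulting in a required sample size of 10.6". Table 2 schedules TUG four times: baseline, mid-intervention, post-intervention and 2 months.

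Statistical methods {20a} covers primary and secondary outcomes together. It first says that efficacy rests on change from the pre-intervention evaluation within each sub-study. It then gives one recipe for three effects (time, group and their interaction): "we employ repeated-measures analysis of variance and repeated-measures analysis of covariance for variables exhibiting a normal distribution". Generalized estimating equations are reserved for variables that are not normal, and significance is judged at P < 0.05. It does not say which of the three effects decides the primary outcome, which visits enter the model, when the covariance version is used, or what the covariate is.

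**The concern.** The endpoint and the sample size point to one comparison with one degree of freedom. The analysis section offers three effects and singles out none. They answer different questions, and most do not concern the pre-to-post difference between arms.

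Two things are at stake. First, a significant result might not concern the primary outcome: a multi-visit interaction can be driven by follow-up, which the plan calls secondary. Second, with about 11 evaluable patients per arm, leaving the deciding test open allows it to be chosen after the results are known. In addition, baseline TUG is collected on everyone but is not named as the covariate, so the precision it offers is not secured.

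**Working it through.** **Inputs.** From Sample size {14}: difference 4.9, SD 4.0, power 80%, alpha 5%, follow-up rate 75%, 30 per sub-study. From Sequence generation {16a}: 1:1 allocation. Assumptions not in the documents: 4.0 is the SD of the change; the unit is seconds; tests are two-sided; visits have equal variance and equal correlation (compound symmetry); the arm differences at mid-intervention and follow-up, and the within-patient correlations, are illustrative.

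**1. The plan's own figure.** Lehr's formula gives 16/(4.9/4.0)² = 16/1.5006 = 10.66, so 11 per arm. With 75% follow-up, 11/0.75 = 14.7, so 15 per arm and 30 per sub-study. This reproduces the plan. (As printed, the square is misplaced: (16/1.225)² would be 170.6. The stated result is nonetheless Lehr's.) Exact two-sample t power at 11 per arm: noncentrality (4.9/4.0)·√(11/2) = 2.873 on 20 df, power 78.0%. At 15 per arm it is 89.9%.

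**2. Interaction on pre and post only.** With two visits, the time-by-group F equals the square of the two-sample t on change. A simulated data set gave 18.02 for both, and the power is the same 78.0%. This form of the planned model tests the primary outcome and matches the sample size.

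**3. Interaction over all four TUG visits.** Let d be the arm difference at each visit. The within-patient error variance is 4.0²/2 = 8. Noncentrality is λ = (n/2)·Σ(d − mean d)²/8, with 3 and 60 df at n = 11.

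| Arm difference, s (pre, mid, post, follow-up) | Σ(d − mean d)² | λ | Probability of P < 0.05 |
|---|---|---|---|
| 0, 2.45, 4.9, 2.45 | 12.005 | 8.25 | 64% |
| 0, 2.45, 4.9, 4.9 | 16.507 | 11.35 | 79% |
| 0, 0, 4.9, 0 | 18.008 | 12.38 | 83% |
| 0, 4.9, 4.9, 4.9 | 18.008 | 12.38 | 83% |
| 0, 4.9, 4.9, 0 | 24.010 | 16.51 | 93% |
| 0, 0, 0, 4.9 | 18.008 | 12.38 | 83% |

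The first five rows share the same 4.9 s difference at post; power runs from 64% to 93%, on both sides of the t-test's 78%. In the last row the primary contrast is zero, yet the test is significant 83% of the time.

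**4. Group main effect, pre and post both as responses.** Baseline has no true arm difference, so the averaged difference is 4.9/2 = 2.45 s. The variance of a patient's mean is [8/(1 − ρ)]·(1 + ρ)/2, which is 12.0, 22.7 and 76.0 for ρ = 0.5, 0.7 and 0.9. Power at 11 per arm is 35%, 21% and 10%.

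**5. Time main effect.** It pools the arms and does not compare them.

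**6. Post-intervention TUG adjusted for baseline.** With equal variances, the change score has variance 2σ²(1 − r) and the adjusted outcome σ²(1 − r²), a ratio of (1 + r)/2. For r = 0.5 the effective SD is 4.0·√0.75 = 3.46 and power at 11 per arm (19 df) is 88%. For r = 0.8 it is 4.0·√0.90 = 3.79 and power is 82%.

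**The case against.** A reader might infer that the planned analysis does not test the primary outcome at all and is not the test that was sized. The documents do not support that. The time-by-group interaction is among the planned effects, and on pre and post alone it is the sized test (step 2). The same section rests efficacy on change from the pre-intervention evaluation. A pre-to-post contrast within a model of more visits would also serve.

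Nor does the article say that four visits are modelled; that TUG is measured four times does not settle it. If change scores are the response, or baseline is the covariate, the dilution in step 4 does not arise. A reader might also infer that a multi-visit interaction generally loses power. It does not: 64% belongs to one chosen profile, and the others computed reach 79-93%.

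Finally, the trial is declared exploratory, and an article may leave the contrast, the visits and the covariate to a full protocol or SAP that is not shown.

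Most of this stands, and it limits the finding. What remains is that the section states a method for the primary outcome, and the two-visit reading that makes it fit has to be supplied by the reader. Change from pre-intervention covers the mid, post and follow-up visits equally well. The exploratory label does not remove the value of one defined primary test, since Explanation for the choice of comparators {6b} sets out to show superiority over an active control.

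**Conclusion.** The concern holds in a limited form. The primary test is not fixed: among the stated effects, only the interaction restricted to pre and post is the comparison that was sized. The others either do not compare arms, may be diluted by baseline, or can be significant through follow-up alone (about 83% for a 4.9 s difference there and none at post). Whether a multi-visit interaction gains or loses power for a post effect depends on the profile, 64% to 93% against 78%.

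These figures rest on 11 evaluable per arm, compound symmetry and 4.0 being the SD of change. The qualitative point does not depend on them. The weight is that of a free improvement, below a must-fix: nothing shows that the planned method cannot test the primary outcome, and the sample size is unaffected.

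**What to change.** In Statistical methods {20a}, state one primary analysis for each sub-study: the between-arm difference in TUG time at the post-intervention visit, adjusted for baseline TUG by analysis of covariance, with one degree of freedom, two-sided 5%, an estimate and a 95% confidence interval. Make the mid-intervention and 2-month contrasts secondary. State that the overall time, group and multi-visit interaction tests are not the efficacy criterion.

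The cost is wording only, settled before the allocation is unmasked. No data are added and the size stays at 30 per sub-study. Baseline adjustment raises power at 11 per arm from 78% to about 82-88%, for assumed correlations of 0.8 to 0.5.
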